### 2.3. Sample Size

The sample size (*n* = 40) was calculated a priori for a mixed repeated-measures design with two groups (control vs. experimental) and two assessment time points (pre- and post-intervention). The calculation assumed a significance level of α = 0.05, a statistical power (1 − β) of 0.80, and an expected small-to-moderate effect size (f = 0.25), with an assumed within-participant correlation of 0.5 and a nonsphericity correction of ε = 1.0. Under these assumptions, a minimum of 34 participants was required, evenly distributed as 17 individuals per group. Considering the potential for participant attrition and to ensure an adequate sample for pre- and post-intervention analyses, an attrition rate of approximately 15–20% was anticipated. Therefore, a total of 40 older adults will be recruited, with 20 participants allocated to the experimental group and 20 to the control group. The flow of participants through each stage of the study will be presented using a adapted CONSORT flow diagram adapted for quasi-experimental studies (Figure 1).

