### 2.8. Statistical Analysis

Data analysis will be performed using IBM SPSS Statistics software, version 30.0. Prior to analysis, data cleaning and coding procedures will be conducted to verify the absence of errors, outliers, or missing values. All statistical analyses will be carried out using a significance level of *p* < 0.05 and a 95% confidence interval.

At an initial stage, a descriptive and exploratory analysis will be conducted to characterize the sample and examine the distribution of the study variables. Sociodemographic variables (including age, sex, educational level, and comorbidities) will be summarized using absolute and relative frequencies for categorical variables, and measures of central tendency and dispersion (mean, median, standard deviation, and interquartile range) for continuous variables. Normality will be assessed using the Shapiro–Wilk test. Based on distributional assumptions, between-group comparisons will be performed using the independent-samples *t*-test for normally distributed continuous variables, the Mann–Whitney U test for ordinal variables or continuous variables with non-normal distributions, and the chi-square test for nominal variables.

To evaluate the effects of the virtual reality intervention, a two-way repeated-measures ANOVA will be conducted to test group-by-time effects (group × time). The primary analysis will follow the intention-to-treat (ITT) principle. A minimum of 20 imputed datasets will be generated, and this number may be increased depending on the proportion of incomplete data. Effect sizes will be estimated using partial eta-squared (ηp^2^) and interpreted as small (0.01), medium (0.06), or large (0.14) [36].

To control for inflation of type I error across secondary endpoints, *p* values for the prespecified secondary outcome analyses will be adjusted using the Holm–Bonferroni sequential procedure. This method was selected because it appropriately controls the family-wise error rate in the presence of multiple comparisons while being less conservative than the traditional Bonferroni correction. The correction will be applied to the secondary outcomes FES-I, ABC, SPPB, and handgrip strength. For the primary outcome, unadjusted *p* values will be reported. For the secondary outcomes, both unadjusted and Holm-adjusted *p* values will be presented, together with effect sizes and 95% confidence intervals [37].

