To control for inflation of type I error across the secondary outcomes, the Holm–Bonferroni sequential correction procedure will be applied to FES-I, ABC, SPPB, and handgrip strength [38,39]. This method was selected because it appropriately controls the family-wise error rate in the presence of multiple comparisons while being less conservative than the traditional Bonferroni correction [38,39]. For the primary outcome, unadjusted *p* values will be reported, whereas for the secondary outcomes both unadjusted and adjusted *p* values will be presented. Regarding statistical power, because the sample size was determined primarily based on the primary outcome, the secondary outcomes will be considered supportive and exploratory. With a statistical power of 80%, the study is expected to be more sensitive to large effects, whereas small effects in the secondary outcomes may not be detectable. Therefore, these findings will be interpreted with caution.

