### 3.2. Secondary Outcomes

#### Concern About Falling

*Falls Efficacy Scale–International (FES-I):*

The Falls Efficacy Scale–International (FES-I) was developed to provide a comprehensive measure of concern about falling, incorporating both physical and social factors, while ensuring suitability for cross-cultural applications. Available evidence strongly supports its use in older adult populations [43]. The FES-I consists of 16 items in which participants rate their level of concern about the possibility of falling in different situations, using a scale ranging from 1 (not at all concerned) to 4 (very concerned). A total score greater than 23 is commonly considered indicative of elevated or clinically relevant concern regarding fall risk [44].

In the present study, is expected on experimental group to show a 3-to-6-point reduction in total FES-I scores, with a lower proportion of participants scoring > 23, reflecting a small-to-moderate effect size (d ≈ 0.40–0.60). This improvement would indicate enhanced perceived self-efficacy and reduced activity restriction due to fear of falling [44].

*Activities-specific Balance Confidence (ABC) Scale:*

The ABC questionnaire consists of 16 items and may be self-administered or applied by a trained evaluator. It is a widely used subjective measure designed to assess balance confidence and the degree of fear of falling experienced by an individual when performing various daily activities, such as moving around the home, ascending or descending stairs, getting into or out of a car, or bending down to pick up objects from the floor, among others [45]. Participants rate their confidence in performing each activity without losing balance or becoming unsteady, generating a total score expressed as percentage, with higher values indicating greater balance confidence.

In this study, changes in total ABC score will be analyzed to evaluate the effect of the intervention on balance-related confidence. A value ≥ 67% has been associated with lower fall risk in community-dwelling older adults and will be considered clinically relevant threshold. Improvements in total score, as well as an increase in the proportion of participants reaching value ≥ 67%, will be interpreted as reflecting enhanced perceived safety and functional confidence during activities of daily living. A small-to-moderate effect size (d ≈ 0.40–0.70) is anticipated,

*Short Physical Performance Battery (SPPB):*

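### Section 2.3 attaches 80% power to a small-to-moderate effect, but the f = 0.25 that gives N = 34 is a 1.0 SD between-group difference in change, which is a large effect

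*Protocol article*

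**What the plan says.** Section 2.3 describes the calculation as one for a "mixed repeated-measures design with two groups (control vs. experimental) and two assessment time points (pre- and post-intervention". Its inputs are "a significance level of α = 0.05, a statistical power (1 − β) of 0.80", then "an expected small-to-moderate effect size (f = 0.25), with an assumed within-participant correlation of 0.5", and a nonsphericity correction of 1.0. The result is 34 participants, 17 per group, raised to 40 for attrition. No TUG difference or standard deviation is given to support f = 0.25.

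Section 2.8 names the matching test: "a two-way repeated-measures ANOVA will be conducted to test group-by-time effects (group × time". Effect sizes will be reported as partial eta-squared, "interpreted as small (0.01), medium (0.06), or large (0.14". The same section remarks: "With a statistical power of 80%, the study is expected to be more sensitive to large effects"; the sentence then turns to small effects in the secondary outcomes.

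Section 3.2 uses the section 2.3 label on another scale. For FES-I the expected change is described as "reflecting a small-to-moderate effect size (d ≈ 0.40–0.60", and for ABC and SPPB the same label goes with d of about 0.40 to 0.70.

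**The concern.** An f value has no fixed meaning in a repeated-measures design. It depends on whether the number of time points and the pre-post correlation are already inside f, or enter the noncentrality parameter separately. In the second case a given f is a much larger effect than the usual label suggests, and the power then belongs to a different effect from the one named.

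This matters for the primary hypothesis. H1 predicts a significant TUG advantage over a control group that, under section 2.7.6, follows the same session schedule with only the modality changed. The Introduction credits this type of exercise with demonstrated benefit. A 1.0 SD advantage over such a comparator is demanding. A reader of section 2.3 who later sees a non-significant H1 could conclude that a small-to-moderate benefit had been ruled out with 80% power.

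**Working it through.** **Inputs.** From section 2.3: two groups, m = 2 time points, alpha = 0.05, power 0.80, f = 0.25, correlation rho = 0.5, epsilon = 1.0, 17 per group. Sidedness is not stated, but the interaction F test has 1 numerator df and so equals a two-sided t test on change scores.

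**Step 1: reproduce N = 34.** For the within-between interaction,

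lambda = f² × N × m × epsilon / (1 − rho) = 0.0625 × 34 × 2 × 1.0 / 0.5 = 8.5, with df 1 and 32.

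The noncentral F gives power 0.807. At N = 32 it is 0.781, so 34 is the smallest even N that reaches 0.80. The other conventions tried do not give 34:

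- lambda = f² × N, without the m/(1 − rho) factor: N = 128
- lambda = f² × (N − 2): N = 130
- f as a between-groups main effect: N = 98

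The protocol's own answer therefore identifies the convention.

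**Step 2: what f = 0.25 means there.** Let delta be the between-group difference in pre-post change and SD the outcome standard deviation. The four interaction cell effects are ±delta/4, so f = delta/(4 × SD) and delta = 4 × 0.25 = 1.0 SD. The SD of change is SD × √(2(1 − rho)) = SD × √1 = SD at rho = 0.5, so delta is also 1.0 SD of change.

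Check: for a t test on change with 17 per group, the squared noncentrality is 1.0² × 17/2 = 8.5, the same lambda. Its power is again 0.807, and a simulation of 20,000 trials gave 0.809.

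**Step 3: place it on the section 2.8 scale.** Partial eta-squared = lambda/(lambda + N) = 8.5/(8.5 + 34) = 0.20, against the large benchmark of 0.14. The medium benchmark of 0.06 fits f = 0.25 only when f is defined from partial eta-squared itself: f²/(1 + f²) = 0.0625/1.0625 = 0.059. That definition needs N = 128, not 34.

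**Step 4: power for the range the protocol elsewhere labels small-to-moderate.** With d the difference in change in outcome-SD units, rho = 0.5 and two-sided 0.05:

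| d | 17 per group | 20 per group | Total N for 80% power |
|---|---|---|---|
| 0.4 | 0.205 | 0.234 | 200 |
| 0.5 | 0.293 | 0.338 | 128 |
| 0.6 | 0.396 | 0.456 | 90 |
| 0.7 | 0.508 | 0.578 | 68 |
| 1.0 | 0.807 | 0.869 | 34 |

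**Step 5: dependence on the correlation (N = 34).**

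| rho | d = 0.4 | d = 0.5 | d = 0.7 |
|---|---|---|---|
| 0.5 (protocol) | 0.205 | 0.293 | 0.508 |
| 0.7 (assumed) | 0.309 | 0.447 | 0.724 |
| 0.8 (assumed) | 0.432 | 0.609 | 0.879 |

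Across these values of d and rho, 80% is exceeded only at d = 0.7 with rho = 0.8, a correlation that the protocol does not assume.

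**The case against.** The strongest defence is that nothing was miscalculated. Section 2.3 discloses f, the correlation, epsilon, alpha and power, so a careful reader can recover what was powered, and the study presents itself as a feasibility study with early effect estimates. This stands as far as it goes: N = 34 is correct and the defect is one of description. Disclosure does not make the label right, though, and the label is what most readers will carry away.

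A second objection is that d of 0.4 to 0.7 is a borrowed yardstick. Those values belong to FES-I, ABC and SPPB, the protocol gives none for TUG, and section 3.2 does not say that they are between-group differences in change. That also stands. The range shows what the label means in this document; it is not a stated target for the primary outcome. The mismatch with the 0.14 benchmark does not depend on it.

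A reader might also infer more than the document supports:

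- **That section 2.8 directly contradicts section 2.3.** Its remark on large effects sits in a discussion of the secondary outcomes, and any study is more sensitive to larger effects. The two sections are at most in tension. Equally, the remark does not correct the claim made for the primary outcome.
- **That the required TUG difference exceeds the 2.3 s measurement-error threshold in section 3.1.** No TUG SD is given, and the 10 to 20 s entry window does not fix one. If the SD were 2 s, 1.0 SD would be 2.0 s. The threshold also applies to an individual's change, not to a difference between group means.
- **That low power for the Holm-adjusted secondary tests is a further fault.** Section 2.8 already treats those outcomes as exploratory and to be read cautiously.

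**Conclusion.** The concern holds as an error of labelling and of the power claim, not of arithmetic. The 80% power belongs to a 1.0 SD between-group difference in pre-post change, with partial eta-squared about 0.20. On the protocol's own scale this is larger than large.

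If small-to-moderate means 0.4 to 0.7 SD, then at the assumed correlation of 0.5 a true benefit of that size would be missed in about half to four-fifths of such trials with 34 completers (1 − 0.51 = 0.49 to 1 − 0.21 = 0.79). These powers rest on the borrowed d range and on the correlation, and higher correlations raise them as shown. They also ignore the group-level allocation described in section 2.2; any clustering would lower them. The 1.0 SD in outcome units follows from f = 0.25 whatever the correlation, but it equals 1.0 SD of change only at 0.5.

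**What to change.** Keep n = 40, the test and alpha. In section 2.3, delete the small-to-moderate label and state instead:

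> 34 completers give 80% power for a between-group difference in TUG change of 1.0 SD (a large effect, partial eta-squared about 0.20), assuming a pre-post correlation of 0.5. Under the same assumption, power for 0.4 to 0.7 SD is about 0.2 to 0.5.

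In section 2.8, commit to reporting the group difference in TUG change in seconds with its 95% CI, and state that a non-significant H1 does not exclude a moderate benefit.

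The cost is a few sentences. Recruitment and design do not change. The price is a less favourable power statement, which fits the study's feasibility aim.

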#### 2.9.2. Retention Rate

The retention rate is defined as the percentage of participants who complete all planned sessions and assessments relative to the total number of individuals who initiate the study. This indicator will be used to evaluate participant retention and continuity throughout the protocol. Based on the planned sample size, a minimum retention rate of 80% is expected for both the experimental and control groups (*n* = 32).

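### Recruiting 40 covers 15% attrition exactly, not the 15–20% that the sample-size section says it anticipates

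*Protocol article*

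**What the plan says.** Section 2.3 (Sample Size) of the protocol article sizes the study for "two groups (control vs. experimental) and two assessment time points (pre- and post-intervention"). The inputs are a 5% significance level, "a statistical power (1 − β) of 0.80", "an expected small-to-moderate effect size (f = 0.25"), and a repeated-measures structure "with an assumed within-participant correlation of 0.5 and a nonsphericity correction of ε = 1.0". From these it concludes that "a minimum of 34 participants was required", split 17 and 17. The step to the recruitment target follows: "an attrition rate of approximately 15–20% was anticipated. Therefore, a total of 40 older adults will be recruited", 20 in each group.

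Two other sections bear on the point. Section 2.8 (Statistical Analysis) plans a group-by-time repeated-measures ANOVA, an intention-to-treat primary analysis and at least 20 imputed datasets. Section 2.9.2 (Retention Rate) states that "a minimum retention rate of 80% is expected for both the experimental and control groups" and gives this as 32 people. It counts as retained only those who complete every planned session and every assessment.

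**The concern.** The target of 40 is presented as the consequence of a range of attrition, so a reader will take it that 34 completers are secured anywhere in that range. If only the lower end is covered, the claimed 80% power is not delivered over the losses the protocol itself expects, and the sample-size statement is more favourable than its figures allow. The 20% end cannot be set aside as remote, since the protocol names it as part of what is anticipated. What is at stake is the accuracy of the stated justification and a small amount of power; the design itself is not in question.

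**Working it through.** **Inputs, all from section 2.3 unless noted.** Two groups (k = 2), two time points (m = 2), f = 0.25, within-participant correlation ρ = 0.5, ε = 1.0, α = 0.05, target power 0.80, minimum 34, attrition 15–20%, recruitment 40. The tested effect, group by time, is from section 2.8.

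**Step 1. Reproduce the minimum of 34.** For the within–between interaction the test is a noncentral F with

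- λ = f² × N × m × ε / (1 − ρ) = 0.0625 × N × 2 / 0.5 = 0.25 N
- df1 = (k − 1)(m − 1) = 1
- df2 = (N − k)(m − 1) = N − 2

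| N | λ | Power |
|---|---|---|
| 32 | 8.00 | 0.781 |
| 33 | 8.25 | 0.795 |
| 34 | 8.50 | 0.807 |
| 40 | 10.00 | 0.869 |

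The smallest N that reaches 0.80 is 34, so the protocol's minimum reproduces exactly.

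**Step 2. Recruits needed to keep 34 completers, N / (1 − d).**

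- 15%: 34 / 0.85 = 40.0. Per group, 17 / 0.85 = 20.0.
- 20%: 34 / 0.80 = 42.5, so 43. Per group, 17 / 0.80 = 21.25, so 22 per group and 44 in total.

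The cruder inflation N × (1 + d) does not rescue the figure. At 20% it gives 34 × 1.20 = 40.8, so 41, or 42 with equal arms (17 × 1.20 = 20.4, so 21 per group).

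**Step 3. Expected completers from 40, 40 × (1 − d).**

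| Attrition | Completers | Per group |
|---|---|---|
| 15% | 34.0 | 17.0 |
| 16% | 33.6 | 16.8 |
| 17% | 33.2 | 16.6 |
| 18% | 32.8 | 16.4 |
| 20% | 32.0 | 16.0 |

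Any attrition above 15% takes the expected number below 34.

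**Step 4. Size of the shortfall at 20%.** Completers: 34 − 32 = 2. Recruits: 43 − 40 = 3, or 44 − 40 = 4 with equal arms. Power among completers: 0.781, which is 0.80 − 0.781 = 0.019 below target and 0.807 − 0.781 = 0.026 below the power at 34.

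**Step 5. Compare with section 2.9.2.** 80% of 40 is 32, the same number as in step 4, but it counts something different. Two sessions a week for 12 weeks make 24 sessions. A participant who misses one of them but returns for the post-intervention TUG is not retained by that definition, yet has complete primary-outcome data. Everyone who is retained has the post-test. So 32 retained means at least 32 analysable for TUG, and possibly more.

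**The case against.** **The planned analysis is not a completer analysis.** Section 2.8 calls for intention to treat with multiple imputation, so all 40 are meant to be analysed and 0.781 is not the power of that analysis. This stands as a qualification: the figure has to be labelled as applying to completers. It does not remove the point. Imputation cannot restore the information in post-tests that were never taken, and section 2.3 itself enlarges the sample so that enough people remain for the pre–post comparison.

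**The range is approximate, the loss is small, and the study is about feasibility and preliminary effects.** All true, and this is why the point is minor. But the approximate wording does not help when only the lowest value in the range works, and the section does rest its sample size on 80% power.

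**A stronger reading is tempting.** A reader might infer that sections 2.3 and 2.9.2 contradict each other: the trial could meet its 80% retention benchmark with 32 people while missing its minimum of 34. The documents do not support that as a contradiction. Retention there requires every session and assessment, so 32 is a lower bound on those with a post-intervention TUG. It is also a descriptive feasibility indicator under the complementary analyses, and nothing in the protocol says that meeting it must guarantee 80% power. For the same reason, raising that retention rate to 85% would be the wrong repair. It would ask 85% of participants to attend every session, which power does not require, and would sit awkwardly beside an anticipated attrition of up to 20%.

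**Conclusion.** The point holds, and it is minor. The minimum of 34 is correct for the stated inputs, and 40 recruits protect it against 15% attrition with no margin. At the 20% end of the stated range, 32 completers remain and power among them is about 78%, roughly two percentage points short of the target.

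The power figures take the protocol's effect size, correlation and independence between participants as given, and assume that losses fall equally on the two groups. They describe completers. I have put no figure on the power of the imputed analysis at 20% loss. The shortfall rests on section 2.3 alone and does not depend on how section 2.9.2 defines retention.

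**What to change.** Keep the recruitment target at 40 and reword section 2.3 to say that it allows for 15% attrition, leaving the 34 required, and that 20% attrition would leave 32 completers (16 per group) and about 78% power among them. This is a wording change. Its only cost is that one stated figure becomes slightly less favourable.

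If the sponsor prefers to keep the claim of cover up to 20%, recruitment would have to rise to 44 (22 per group), four more people.

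Leave the all-sessions retention rate in section 2.9.2 as it is. If a feasibility benchmark is to be tied to the sample-size minimum, add a separate one for completion of the post-intervention TUG, set at 34 of 40 (17 of 20 per group). That needs a new one-line definition and no new data.

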### 2.4. Participant Recruitment

Participant recruitment will be conducted across the different groups affiliated with primary health care (PHC) services in the municipality of San Pedro de la Paz, Biobío Region, Chile.

The recruitment process will be carried out by trained research support staff. Initial contact will be made by telephone with the representatives of the participating groups, followed by the coordination of in-person visits to the locations where group activities take place. During these visits, older adults will be invited to participate in the study and will be provided with clear and comprehensible information regarding the study objectives, the general characteristics of the virtual reality (VR) intervention, its duration, and the associated assessment procedures. Emphasis will be placed on the voluntary nature of participation and on the participants’ right to withdraw from the study at any time without consequences.

Older adults who express interest in participating will be assessed to verify compliance with the established eligibility criteria. Final inclusion in the study will occur only after the informed consent form has been signed, ensuring adherence to the ethical principles of autonomy, confidentiality, and safety for older participants.

To safeguard confidentiality and anonymity, participant identification data will be coded using alphanumeric identifiers. These codes will also be used to differentiate between pre- and post-intervention measurements.

